### Interventions

All enrolled subjects received supragingival scaling using ultrasonic scalers, oral hygiene instruction (OHI) including tooth brushing with the modified Bass technique and interdental cleaning with interdental brushes or dental floss. They are submitted to a complete periodontal clinical assessment. Subsequently, the upper and lower teeth of each subject are randomly allocated to the following therapeutic groups: (1) ultrasonic subgingival scaling combined with manual root planing group; (2) ultrasonic subgingival debridement group. The treatment is carried out at the Periodontology Department, Peking University School and Hospital of Stomatology. The treatment is performed by an experienced periodontist who has been calibrated before the trial. The treatment is completed under local anesthesia in two sessions of approximately 1 h, distributed over a period of 7 days. Ultrasonic subgingival scaling is performed using magnetostrictive ultrasonic device (Charlotte, North Carolina Dentsply, model number: Gen-130B, 25 kHz, USA). Manual root planing is performed using Gracey curettes (conventional and mini-fives) numbers 5/6, 7/8, 11/12 and 13/14 (Hu-Friedy, Shanghai, China). At the end of each session, the clinical coordinator evaluates the effectiveness of treatment using the outcome “smoothness of the scaled roots.” All subjects will receive personalized OHI after treatment until the end of the study (24 weeks post therapy).

### Examination

#### Baseline examination

After the subjects have been included, plaque index (PLI), probing depth (PD), clinical attachment loss (CAL), bleeding index (BI), furcation involvement (FI) and mobility are tested before treatment by a calibrated examiner (not the therapist) who has been trained to adequate levels of accuracy and reproducibility.

### Examination during the follow-ups

#### Follow-up

All subjects will be recalled for follow-up at weeks 2, 4, 12 and 24 after the treatment. At weeks 4, 12 and 24 after the treatment, PLI, PD, CAL, BI, FI and mobility will be examined by a calibrated examiner. Any complications will be documented. Besides, subjects will complete a Visual Analog Scale/Score (VAS) to evaluate pain and sensitivity during the 2 and 4 weeks after treatment.

### Primary parameters

The primary parameters of this trial are PD, CAL and BI.

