### Sample size

The sample size of this trial is calculated based on the formula:
$$ \kern13.25em N=\left[\frac{\left(z\frac{\alpha }{2}+ z\beta \right)\sigma }{\delta}\right]2\left(\frac{1}{Q1}+\frac{1}{Q2}\right). $$

According to the preliminary experiment results and data analysis from currently published articles, the difference of PD with and without root planing (*δ*) is around 0.3 mm and the standard deviation in groups (*σ*) is around 0.2 mm.

If the inspection level (*α*) is set at 0.05 and the power of test (*β*) is set at 90%, then 18 subjects will be required for each group. Given that loss to follow-up is around 10%, this study will require 20 subjects for each group. Consequently, this trial will require at least 40 subjects in all.

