### Statistical analysis

A Shapiro-Wilk test and Levene variance homogeneity test will be performed to test the normality and variance equality, respectively. Continuous normally distributed data will be expressed as mean ± standard deviation (SD), and non-normally distributed data as median (lower to upper quartile). A paired-samples *T* test or two-related-samples test will be used to identify any differences between groups. Statistical significance difference will be set as *P* value of less than 0.05. Data analyses will be performed using SPSS software.

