## Discussion

Periodontitis is strongly associated with the presence of bacterial biofilms and dental calculus on root surfaces. Hence, the ultimate goal of nonsurgical pocket/root instrumentation is to render the root free from microbial deposits and calculus. The success of periodontal treatment depends on the removal of deposits from the root surface [27–30]. All kinds of studies performed in different models and under different conditions have indicated that neither manual nor mechanical instruments are superior in removing subgingival deposits [31–37]. There was no significant difference in the changes of PD, CAL and BOP between manual subgingival debridement and ultrasonic subgingival debridement.

Previous studies demonstrated that hand instrumentation curettage created the smoothest root surface, whereas mechanical instruments, such as the ultrasonic scaler, tended to roughen the root surface [38]. Cobb found that manual curettes were more technique-sensitive and time-consuming [39]. The old concept of infected cementum removal in order to provide the root surface biocompatible for soft tissue healing [11, 12] has been questioned by various studies [15, 16]. The utilization of ultrasonic devices for subgingival debridement offers a less aggressive and a more comfortable therapeutic method for both the patient and therapist. But, some research has shown that the comparison between manual instruments and ultrasonic scalers did not show an advantage over machine-driven instruments [20], and tissue trauma was similar in both instruments [40]. Therefore, the necessity of manual root planing cannot be completely denied. Hand instrumentation has been recommended to smooth the root surface after ultrasonic debridement as the final finishing procedure in the treatment of periodontitis-affected roots [41]. At present, root planing is no longer used to emphasize the deliberate removal of cementum, but to contribute to the removal of subgingival plaque.

This study thus intends to evaluate in vivo the effectiveness of ultrasonic subgingival scaling combined with manual root planing and ultrasonic subgingival debridement alone in the nonsurgical treatment of periodontitis with a split-mouth design after 1, 3 and 6 months. We hope that the results could lead to an advanced treatment strategy of periodontitis with an ideal clinical outcome.

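### Three unranked primary parameters, three visits and one unadjusted 0.05 threshold, with a sample size built on probing depth alone and no rule for the primary conclusion

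*Protocol article*

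**What the plan says.** - **Primary parameters:** "The primary parameters of this trial are PD, CAL and BI". None is ranked above the others.
- **Follow-up:** "At weeks 4, 12 and 24 after the treatment, PLI, PD, CAL, BI, FI and mobility will be examined by a calibrated examiner". No visit is called primary.
- **Discussion:** effectiveness is to be evaluated "with a split-mouth design after 1, 3 and 6 months", again with the three times on an equal footing.
- **Statistical analysis:** a paired-samples T "test or two-related-samples test will be used to identify any differences between groups", judged at a P "value of less than 0.05". The section gives no order of testing, split of alpha or requirement that several parameters succeed together.
- **Sample size:** the effect is "the difference of PD with and without root planing", about 0.3 mm with a standard deviation of about 0.2 mm. Alpha is 0.05 (two-sided, since the formula uses alpha/2) and power is 90%. CAL, BI and the visit do not enter.
- **Objectives and hypotheses:** the primary hypothesis, that root planing is an important step, is tied to no parameter or visit.

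**The concern.** The Primary parameters and Sample size sections describe different trials. One has three co-equal primaries. The other has a single PD comparison at one alpha of 0.05. With three visits, up to nine between-side comparisons can be called primary, and no rule turns their results into a conclusion.

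Two operating characteristics depend on that missing rule. If one significant result is enough, the error rate of the primary claim is above 5%, and the parameter and visit that carry it can be picked after the results are known. If all parameters must succeed, the stated power is not the power of the trial. The trial is meant to guide dentists on whether manual root planing is needed, so an isolated result, such as BI at week 4, should not be presentable as confirmation of the primary hypothesis.

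**Working it through.** **Inputs from the protocol.** Three primary parameters; three post-treatment visits; two-sided alpha 0.05 per test; PD difference 0.3 mm, SD 0.2 mm, power 90%, 18 per group.

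**Assumed input.** The protocol gives no correlation between the parameters or the visits. What matters is the correlation between the within-patient side differences, not between the raw measurements. A range of 0 to 0.95 was used.

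**1. The plan's own figure.** The printed formula with equal allocation (Q1 = Q2 = 0.5) gives N = [(1.960 + 1.282) × 0.2 / 0.3]² × (2 + 2) = 4.670 × 4 = 18.68. So 18 is close to the formula's total over both groups, not to a per-group number (the two-means formula gives 9.34, hence 10 per group). That is a separate matter. Here it shows only that the calculation uses PD alone, at a single 0.05.

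**2. Any one result counts, independent tests.** Family-wise error = 1 − 0.95^k.
- k = 3 (one visit): 1 − 0.8574 = 14.3%.
- k = 9 (three visits): 1 − 0.6302 = 37.0%.

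**3. Any one result counts, correlated tests.** Simulated two-sided z tests, one million draws per setting. For nine tests, the correlation shown applies separately between parameters and between visits.

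| Assumed correlation | Three tests, one visit | Nine tests |
|---|---|---|
| 0 | 14.3% | 37.0% |
| 0.5 | 12.5% | 29.4% |
| 0.7 | 10.9% | 22.5% |
| 0.9 | 8.4% | 13.6% |

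In an uneven case (PD–CAL 0.8, BI with either 0.3), nine tests give 28.5%, 25.0% and 19.5% at visit correlations of 0.5, 0.7 and 0.9. In the most extreme setting, with every pair of tests correlated 0.95, three tests give 7.3% and nine give 9.9%. No setting reaches 5% or less.

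**4. False results favouring root planing only.** The nominal rate per test is 2.5%.
- Independent tests: 1 − 0.975³ = 7.3%; 1 − 0.975⁹ = 20.4%.
- Nine tests with both correlations at 0.5, 0.7 and 0.9: 14.8%, 11.3% and 6.8%.

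This is about half the two-sided rate.

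**5. All three must succeed at one named visit.** The chance of a false overall success is at most 5%, so there is no inflation. Joint power cannot exceed the PD power and depends on CAL and BI inputs that the document does not give. As an illustration only: if each parameter had 90% power and the results were independent, joint power would be 0.9³ = 72.9%.

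**6. Cost of an adjustment, using the document's PD inputs.** Two-means formula: n per group = 2 × (z for alpha/2 + 1.282)² × (0.2/0.3)².
- Alpha 0.05/3: 2 × (2.394 + 1.282)² × 0.4444 = 12.01, rounded up to 13.
- Alpha 0.05/9: 2 × (2.773 + 1.282)² × 0.4444 = 14.6, rounded up to 15.

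Both lie below the stated 18 per group.

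**The case against.** The case on the other side has four parts.

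**The document is a condensed article.** A SAP may exist, and adjustment methods, testing order and the handling of repeated visits are commonly left to it. This stands as far as it goes: the lack of an adjustment method is not, alone, a finding. But the choice of primary endpoint and visit belongs in the protocol, and this one states three primaries against a sample size for one.

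**No any-one-wins rule is written down.** The Follow-up section is an examination schedule, and the Statistical analysis section gives a generic test and threshold. A reader might infer that significance on any of nine tests confirms the hypothesis. The document neither says this nor rules it out. The accurate statement is that no rule is given, so every error rate above is conditional.

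**The large figures are easily overread.** A reader might take 11–37% as the trial's chance of falsely concluding that root planing helps. That is not supported. The 37% is a ceiling that needs independence between repeated measurements in the same mouths. The 11% is a three-test figure at one visit with an assumed correlation of 0.7, and is not a floor. Both count false results in either direction, whereas the stated hypothesis favours root planing.

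**The design is not threatened.** On the PD inputs, even Bonferroni over nine tests fits within the planned number. This also stands: the defect lies in the definition of the primary endpoint, not in the size of the trial. Choosing week 24, and fixed sequence or Holm, is a judgement, since the document singles out no visit.

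**Conclusion.** The point holds in conditional form. Three unranked primaries, three unranked visits and one unadjusted threshold do not match a sample size for PD at a single 0.05, and no rule connects them to the primary conclusion.

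Under an any-one-wins reading, every setting examined exceeds the nominal level. The most plausible range for nine tests is roughly 14–29% two-sided, and 8–13% for three tests at one visit, at assumed correlations of 0.9 to 0.5. Under an all-must-win reading at a named visit, type I error is sound but the 90% power is not that of the trial. Neither reading delivers both the error rate and the power that the Sample size section implies. The document does not support the claim that the trial will run at any particular inflated rate, because the correlations are assumed and the decision rule is unstated.

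**What to change.** Before unblinding, amend the protocol, the SAP if there is one, and the registry entry as follows.

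- Name one primary endpoint at one visit. The choice most consistent with the document is the between-side difference in PD, which sized the trial, at week 24, which ends follow-up. Test it at two-sided 0.05.
- If PD is significant, test CAL and BI at the same visit under a prespecified procedure, either in fixed sequence or by Holm.
- Report weeks 4 and 12 as supportive, with estimates and confidence intervals.
- If the investigators prefer to keep three co-primaries, state whether one or all must succeed, name the visit, and redo the alpha or power calculation accordingly.

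The cost is wording. The first option adds no patients or visits, and the alpha already used for PD is unchanged. The downside is that an isolated significant CAL, BI or early-visit result can no longer be called a primary success.

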### Secondary parameters

The secondary parameters of this trial include PLI, FI, mobility and VAS to evaluate pain and sensitivity after treatment.

### Sample size

The sample size of this trial is calculated based on the formula:
$$ \kern13.25em N=\left[\frac{\left(z\frac{\alpha }{2}+ z\beta \right)\sigma }{\delta}\right]2\left(\frac{1}{Q1}+\frac{1}{Q2}\right). $$

According to the preliminary experiment results and data analysis from currently published articles, the difference of PD with and without root planing (*δ*) is around 0.3 mm and the standard deviation in groups (*σ*) is around 0.2 mm.

If the inspection level (*α*) is set at 0.05 and the power of test (*β*) is set at 90%, then 18 subjects will be required for each group. Given that loss to follow-up is around 10%, this study will require 20 subjects for each group. Consequently, this trial will require at least 40 subjects in all.

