The primary objective of scaling and root planing is to restore gingival health by completely removing elements that provoke gingival inflammation (i.e., biofilm, calculus and endotoxin) from the tooth surface. A large amount of in vivo and in vitro research has been conducted to compare ultrasonic and manual instruments, and it was found that there was not much difference between them in clinical effects, changes in microflora and root surface characteristics [20–25]. In fact, there is still a lack of research evidence comparing the clinical effects of ultrasonic subgingival scaling with or without manual root planing. On the one hand, it is difficult to distinguish subgingival scaling from root planing in traditional manual operation; on the other hand, there are fewer dentists using manual subgingival scaling and root planing. Therefore, this study is devoted to comparing the clinical effect of ultrasonic subgingival debridement and ultrasonic subgingival scaling combined with manual root planing in the nonsurgical treatment of periodontitis, which, taking the implementation of root planing as the only variable, is more in line with the clinical situation, hoping to provide some valuable reference for dentists.

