## Methods/design

### Overview

The study is a prospective, single-center, split-mouth randomized controlled trial. Forty patients who have periodontitis and are in need of periodontal treatment will be recruited. The assessments, interventions and follow-ups will be performed at Peking University School and Hospital of Stomatology (Beijing, China). This study has been approved by the Ethics Committee of Peking University School and Hospital of Stomatology (PKUSSIRB-201734032) and registered in the International Clinical Trials Registry Platform (ICTRP) under the ID: ChiCTR1800017122.

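### The sample size paragraph treats a two-group total as a per-group number and doubles it for a split-mouth design, so the stated 90% power is wrong; on the stated inputs the trial is oversized for PD.

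*Protocol article*

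**What the plan says.** The Sample size section gives a formula containing the factor (1/Q1 + 1/Q2) and does not define Q1 or Q2. For PD, the difference with and without root planing "is around 0.3 mm and the standard deviation in groups" is put at about 0.2 mm. Alpha is 0.05 and power 90%. The section concludes "then 18 subjects will be required for each group", raises this to 20 per group for about 10% loss to follow-up, and ends: "Consequently, this trial will require at least 40 subjects in all".

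The Overview describes a different structure: "The study is a prospective, single-center, split-mouth randomized controlled trial", with forty patients. The sections on randomization and on interventions place test and control quadrants in the same mouth. The Statistical analysis section matches that design: a paired t-test or a "two-related-samples test will be used to identify any differences between groups".

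**The concern.** Two steps look wrong. First, a formula with (1/Q1 + 1/Q2) and equal fractions returns the total over two independent groups, yet the text reads its result as the size of each group. Second, going from 20 per group to 40 people treats the arms as different patients, whereas here every patient is in both arms. The variance is also the one for independent groups: the paragraph uses the SD within groups, while the planned paired test depends on the SD of the within-patient difference.

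At stake is whether the stated size and power describe this trial. They justify how many patients are enrolled, and a reader will use them to interpret a null result or a small significant one.

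**Working it through.** **Inputs, all from the Sample size section unless noted.** δ = 0.3 mm; σ = 0.2 mm within groups; α = 0.05, two-sided because the formula uses z at α/2; power 90%; loss 10%. Design and test come from the Overview and Statistical analysis sections. Assumptions: the 2 after the bracket is an exponent flattened in the text, and Q1 = Q2 = 0.5. The correlation ρ between the two sides of a mouth is not given, so a range is shown.

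**1. The plan's own figure.** N = [(z_α/2 + z_β)σ/δ]² × (1/Q1 + 1/Q2).

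- (1.960 + 1.2816)² = 10.507
- 10.507 × (0.2/0.3)² = 4.670
- 4.670 × (1/0.5 + 1/0.5) = 4.670 × 4 = 18.68

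This is the only route with the bracket squared that leads to 18, and it is a total. It should round up to 19, not down. Per group it is 18.68/2 = 9.34, so 10 (11 by the two-sample t-test). If instead Q1 = Q2 = 1 and N is per group, the factor is 2 and the result is again 4.670 × 2 = 9.34. Other settings do not give 18 per group either: two-sided 95% power gives 12 and one-sided 90% power gives 8.

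**2. What 18 per group would deliver.** For two independent arms with a standardised difference of 0.3/0.2 = 1.5, 18 per group gives 99.2% power by the two-sample t-test, not 90%.

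**3. The loss step.** 18/0.9 = 20 is correct arithmetic applied to the wrong quantity.

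**4. The doubling.** In a split-mouth trial, 20 observations per arm come from 20 patients. Forty patients give 40 observations per arm, and about 40 × 0.9 = 36 complete pairs.

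**5. The paired calculation on the same inputs.** SD_d = σ√[2(1 − ρ)] and n = (z_α/2 + z_β)² SD_d²/δ², then corrected for the t distribution. SD_d cannot exceed 2σ = 0.4 mm, its value at ρ = −1.

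| ρ (assumed) | SD_d (mm) | n, normal formula | n, paired t, 90% power | Power with 36 pairs |
|---|---|---|---|---|
| 0.5 | 0.200 | 4.67, so 5 | 7 | above 99.99% |
| 0 | 0.283 | 9.34, so 10 | 12 | above 99.99% |
| −1 (extreme) | 0.400 | 18.68, so 19 | 21 | 99.2% |

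No correlation brings the power of 36 pairs down to 90% while σ = 0.2 holds.

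**6. What 36 pairs can carry.** Solving the paired t-test for 90% power at 0.3 mm gives SD_d of about 0.54 mm. That exceeds the 0.4 mm ceiling implied by σ = 0.2.

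**The case against.** The strongest reply is that nothing is endangered: both errors enlarge the trial, and even at the worst correlation 36 pairs give 99.2% power for PD. This stands, and it sets the weight of the point.

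One might also say that Q1, Q2 and the exponent are guesses. They are assumptions, but the alternative reading of Q1 and Q2 gives 9.34 per group, so 18 per group is not rescued. Another defence is that the two groups are the aggressive and chronic periodontitis strata of the inclusion criteria, which would explain 20 + 20. But the randomization section uses the word for the treatment arms, δ is the contrast with and without root planing, and the number 18 would still be unexplained.

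A reader might infer three stronger things that the document does not support.

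- That the trial may be underpowered for PD. At 36 pairs, power would be 83% if SD_d were 0.6 mm and 59% if it were 0.8 mm. Both values are impossible under σ = 0.2 and require σ itself to be wrong, which nothing in the document shows. Nor is the power simply unknown, because σ bounds SD_d.
- That the source of δ and σ contradicts the Background, which says "there is still a lack of research evidence comparing the clinical effects of ultrasonic subgingival scaling with or without manual root planing". The sample size inputs rest on preliminary results as well as published articles, and a pilot alongside sparse literature is consistent with that sentence.
- That a standardised difference of 1.5 is implausible, or that a missing time point for δ is an error. The first is a judgement that no figure in the document tests; the second is a detail an article may leave to the full protocol.

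**Conclusion.** The concern holds as a correction of a stated figure. Eighteen per group at 90% power does not follow from the protocol's inputs under either reading of Q1 and Q2, and 20 per group does not become 40 people in a split-mouth trial. On those inputs the paired test needs 7 to 21 patients for ρ from 0.5 down to −1, against 40 planned. About 36 completers give at least 99.2% power, and above 99.99% when ρ is 0 or more.

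This rests on the bracket being squared, on a normally distributed within-patient difference, and on σ = 0.2 mm being the SD in each arm as stated. The calculation concerns PD only; the section gives no inputs for CAL or BI. The error misdescribes the trial's size and power but does not threaten the PD comparison.

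**What to change.** Rewrite the one paragraph and leave the target at 40 patients.

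- Delete the per-group wording and the step from 20 to 40.
- Replace the formula with n = (z_α/2 + z_β)² SD_d²/δ², with a t correction, and state the SD of the within-patient difference and its source.
- Restate what the planned number delivers, for example: 40 patients, of whom about 36 are expected to be evaluable, give about 90% power to detect a 0.3 mm difference in PD if the SD of the within-patient difference is at most about 0.54 mm.
- Add a short table of power with 36 pairs: above 99.99% at SD_d 0.20 and 0.283 mm, 99.2% at 0.40, about 90% at 0.54, 83% at 0.60 and 59% at 0.80. Label the values above 0.40 mm as assumptions that go beyond the stated σ.

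The cost is rewording. Recruitment, allocation and the planned paired test do not change.
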